## Abstract

**Background:**

We are performing a combined randomised and observational study comparing internal fixation to non-surgical management for common wrist fractures in older patients. This paper describes the statistical analysis plan.

**Methods/design:**

A Combined Randomised and Observational Study of Surgery for Fractures In the distal Radius in the Elderly (CROSSFIRE) is a randomised controlled trial comparing two types of usual care for treating wrist fractures in older patients, surgical fixation using volar locking plates and non-surgical treatment using closed reduction and plaster immobilisation. The primary aim of this comparative-effectiveness study is to determine whether surgery is superior to non-surgical treatment with respect to patient-reported wrist function at 12 months post treatment. The secondary outcomes include radiographic outcomes, complication rates and patient-reported outcomes including quality of life, pain, treatment success and cosmesis. Primary analysis will use a two-sample *t* test and an intention-to-treat analysis using the randomised arm of the study. Statistical analyses will be two-tailed and significance will be determined by *p* < 0.05. Sensitivity analyses will be conducted to assess for differences in intention-to-treat, per-protocol and as-treated analyses. Sensitivity analyses will also be conducted to assess selection bias by evaluating differences in participants between the randomised and observational study arms, and for bias relating to any missing data. An economic analysis will be conducted separately if surgery is shown to provide superior outcomes to a level of clinical significance.

**Discussion:**

This statistical analysis plan describes the analysis of the CROSSFIRE study which aims to provide evidence to aid clinical decision-making in the treatment of distal radius fractures in older patients.

**Trial registration:**

CROSSFIRE was approved by The Hunter New England Human Research Ethics Committee (HNEHREC Reference No: 16/02/17/3.04). Registered on 22 July 2016 with The Australian and New Zealand Clinical Trials Registry (ANZCTR Number; ACTRN12616000969460).

This manuscript is based on v.11 of the statistical analysis plan. A copy of v.11, signed by the chief investigator and the senior statistician is kept at the administering institution.

## Introduction

### Background

Fractures of the distal radius are the most common fractures presenting to emergency departments and orthopaedic surgeons [1]. These fractures are more common in older people (due to osteoporosis and increased risk of falls) and the incidence in older people is increasing [1]. Considerable practice variation exists in the management of distal radius fractures in the elderly in Australia [2], with two common methods being closed reduction (manipulation of the arm to realign the fracture) with cast immobilisation, and open reduction (surgical exposure and direct realignment of the fracture) and fixation with plate and screw. Open reduction and (volar locking) plate fixation has become the most common form of surgical treatment provided [3]. While there is evidence showing no significant advantage for some forms of surgical fixation over closed treatment, and no difference between different surgical techniques [4–16], there is a lack of evidence comparing the two most common treatments used in Australia, initial treatment with volar locking plate fixation versus closed reduction and cast immobilisation. Surgical management of these fractures involves significant costs (implant costs, medical costs, hospital costs) and risks (infection, implant failure, general surgical risks) compared to non-surgical management (closed reduction and cast immobilisation in the emergency department). Therefore, high-level evidence comparing the current treatment alternatives (plate fixation versus casting) is required in order to address practice variation, justify or avoid costs, and to provide the best clinical outcome for patients with these common fractures.

The CROSSFIRE study protocol was published in 2017 [17]. This statistical analysis plan (SAP) was prepared in accordance with published guidelines [18] on the content of SAPs and was written with input from members of The CROSSFIRE Study Group.

### Purpose of the analyses

The primary and secondary aims of the study are to determine whether surgical treatment (volar-locking-plate fixation) is superior to non-surgical treatment (closed reduction and cast immobilisation) with respect to both effectiveness and safety for adults aged 60 years and older with dorsally displaced distal radius fractures.

The results of the trial will be published in a peer-reviewed journal and will be disseminated via various forms of media. The results will be incorporated in clinical practice guidelines produced by professional bodies.

## Methods/design

### Design

CROSSFIRE is a prospective, multi-centre study with 19 sites in Australia and New Zealand. The study includes a randomised, comparative-effectiveness trial and a parallel observational study; eligible patients were invited to participate in the randomised trial in which their treatment was randomised to surgical or non-surgical treatment. Eligible patients who declined to participate in the randomised study were invited to join the observational study. Participants in the observational study received standard care (one of the two treatment arms in the randomised trial) according to patient and surgeon preference and had the same outcomes measured at the same timepoints as those participating in the randomised trial.

We included an observational ‘preference’ arm that followed non-randomised patients in a similar manner to randomised participants to investigate potential selection bias and provide information on the generalisability of the study [19]. This study design has been used in surgical trials [20] and has been recommended as a model for trials of surgery versus non-surgical treatment where recruitment rates are expected to be lower than for other randomised controlled trials (RCTs) [21].

### Study population

Three hundred participants provided consent and were recruited to CROSSFIRE from 19 participating hospital sites: 164 participants in the randomised trial and 136 in the observational study. No patients declined participation in the observational study.

### Inclusion criteria

Age 60 years or olderDisplaced distal radius fracture, classified according to the Association for the Study of Internal Fixation/Orthopaedic Trauma Association (AO/OTA) [22] 23A (extra-articular distal radius fracture) or 23C (complete articular distal radius fracture). Displacement parameters include more than 10° dorsal angulation, referenced off a line perpendicular to the shaft of the radius or more than 3 mm shortening or more than a 2-mm articular step prior to reductionMedically fit for surgeryIndependent living (including hostel accommodation)Low-energy injury (fall from less than 1 m)Available for follow-up for 12 months

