### Randomisation and allocation

Randomisation occurred immediately after consent was gained by the recruiting orthopaedic team, within 1 week of the date of the injury. The orthopaedic team member contacted a central computer-based randomisation service by telephone. Participants were randomised using the method of minimisation. Randomisation was stratified by site, and minimisation, adjusting for gender and age (60–74 years and > 74 years), was employed as recommended by the National Health and Medical Research Centre (NHMRC) Clinical Trials Centre which provided the randomisation service.

Given the nature of the comparisons (surgery versus no surgery), it was not possible to blind the surgeon (study) investigators or participants. While this increases the risk of performance and detection bias, every effort was made to ensure that treatment, other than the interventions under study was otherwise identical in both groups. The primary outcome (PRWE score at 12 months) was collected from participants by blinded researchers, by telephone.

The statistician and the investigators conducting the analysis will remain blinded to the treatment groups. The dataset will be de-identified and treatment allocation will be masked using dummy group names (for example, Group A and Group B). De-identification and masking will be performed by an independent investigator who is not associated with the analysis. Masking of treatment allocation will be maintained until the statistical analysis and interpretation has been completed and two versions of the manuscript have been prepared and agreed to by all authors.

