### Statistical analysis

#### Analysis principles

Data will be analysed using statistical analysis package SAS (SAS Institute Inc., Cary, NC, USA) and R statistical computing software [40].

Recruitment for CROSSFIRE concluded in January 2019. The final analysis will commence after the 12-month data collection is complete. The de-identified data-set will be inspected for missing data and data quality.

Study outcomes produce both continuous and categorical data. Continuous data will be inspected for normality. Continuous data will be presented by mean values and standard deviations (SDs) as well as mean difference (MD) and 95% confidence interval (CIs) (see Tables 4 and 5 as examples) if normally distributed, otherwise by median and interquartile range.

**Table 4 Tab4:** Secondary outcomes at 3 months for the randomised group

Outcome		Randomised		
		Surgical (*n*=__)	Non-surgical (*n*=__)	MD (95%CI) or odds ratio (95%CI)
PRWE, mean (SD)				
ED-5D-5L, mean (SD)	EQ-UI			
	EQ-VAS			
Pain on NRS (0-10)				
Patient-reported treatment success n(%)	Very successful			
	Successful			
	Neutral			
	Unsuccessful			
	Very unsuccessful			
Therapy utilisation up to 3 months (Yes/No) n(%)				
Therapy utilisation at 3 months (Yes/No) n(%)				
Radiographic measures, mean (SD)	Dorsal angulation (degrees)			
	Radial tilt (degrees)			
	Ulnar variance (mms)			
	Articular step (mms)

**Table 5 Tab5:** Secondary outcomes at 3 months for the observational group

Outcome		Observational		
		Surgical (*n*=__)	Non-surgical (*n*=__)	MD (95%CI) or odds ratio (95%CI)
PRWE, mean (SD)				
ED-5D-5L, mean (SD)	EQ-UI			
	EQ-VAS			
Pain on NRS (0-10)				
Patient-reported treatment success n(%)	Very successful			
	Successful			
	Neutral			
	Unsuccessful			
	Very unsuccessful			
Therapy utilisation up to 3 months (Yes/No) n(%)				
Therapy utilisation at 3 months (Yes/No) n(%)				
Radiographic measures, mean (SD)	Dorsal angulation (degrees)			
	Radial tilt (degrees)			
	Ulnar variance (mms)			
	Articular step (mms)			

Categorical data will be summarised according to frequency (*n*) and incidence (%) (see Table 5). Comparison between treatment groups will be tested using chi-squared and odds ratio with 95% CI.

Comparisons between treatment groups will be tested at the two-sided, 5% significance level. *P* values will be reported to three decimal places if *P* > 0.001. *P* values < 0.001 will be reported as < 0.001. Means and SDs will be reported to one decimal place.

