### Secondary analysis

Outcomes for the randomised group and the observational group will be analysed and represented separately. Outcomes gathered at 3 months will be displayed for the randomised group (see Table 4) and for the observation group (see Table 5). Outcomes gathered at 12 months will be displayed for the randomised group (see Table 6) and for the observational group (see Table 7). Continuous outcomes will be reported by mean values as well as the MDs and 95% CIs. Categorical outcomes will be reported by frequency, incidence and odds ratios.

**Table 7 Tab7:** Primary and secondary outcomes at 12 months for the observational group

Outcome		Observational		
		Surgical (*n*=__)	Non-surgical (*n*=__)	Mean difference (95%CI)
PRWE				
DASH				
ED-5D-5D, mean (SD)	EQ-UI			
	EQ-VAS			
Pain on NRS (0-10)				
Patient-reported treatment success n(%)	Very successful			
	Successful			
	Neutral			
	Unsuccessful			
	Very unsuccessful			
Patient-reported bother with appearance n(%)	Not at all			
	Bothered a little			
	Bothered moderately			
	Very bothered			
	Extremely bothered			
Radiographic measures, mean (SD)	Dorsal angulation (degrees)			
	Radial tilt (degrees)			
	Ulnar variance (mms)			
	Articular step (mms)			

The MDs of PRWE measured at 3 months between the surgical and non-surgical groups will be tested using two-sample *t* tests. The MDs of DASH measured at 12 months between the surgical and non-surgical groups will be tested using two-sample *t* tests.

Physical therapy utilisation up to and at 3 months will be analysed. If surgical treatment is shown to be superior, a cost-effectiveness analysis will be conducted incorporating therapy utilisation and published separately to this analysis. For the purpose of this analysis, therapy utilisation up to 3 months (Yes/No) and ongoing therapy utilisation at 3 months (Yes/No) will each be reported in terms of frequency, incidence and odds ratio between each treatment group. See Tables 3 and 4 as examples.

Complications will be reported in terms of frequency, incidence and the odds ratio between each treatment group (see Tables 8 and 9 as examples). Odds ratio will be calculated based on the number of participants for whom data is available.

**Table 8 Tab8:** Complications for randomised group

Complication; frequency (incidence)	Randomised group		
	Surgical (*n* = _)	Non-surgical (*n* = _)	Odds ratio (95% CI)
Deep infection	*n* (%)	*n* (%)	
Reoperation	*n* (%)	*n* (%)	
Neuropathy	*n* (%)	*n* (%)	

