Tendon irritation requiring treatment	*n* (%)	*n* (%)	
Tendon rupture	*n* (%)	*n* (%)	
Fracture non-union at 6 months	*n* (%)	*n* (%)	
Implant failure	*n* (%)	*n* (%)	
CRPS	*n* (%)	*n* (%)	
Death	*n* (%)	*n* (%)	
Any complications	*n* (%)	*n* (%)	

*CI* confidence interval, *CRPS* chronic regional pain syndrome

**Table 9 Tab9:** Complications for observational group

Complication; frequency (incidence)	Randomised group		
	Surgical (*n* = _)	Non-surgical (*n* = _)	Odds ratio (95% CI)
Deep infection	*n* (%)	*n* (%)	
Reoperation	*n* (%)	*n* (%)	
Neuropathy	*n* (%)	*n* (%)	
Tendon irritation requiring treatment	*n* (%)	*n* (%)	
Tendon rupture	*n* (%)	*n* (%)	
Fracture non-union at 6 months	*n* (%)	*n* (%)	
Implant failure	*n* (%)	*n* (%)	
CRPS	*n* (%)	*n* (%)	
Death	*n* (%)	*n* (%)	
Any complications	*n* (%)	*n* (%)	

*CI* confidence interval, *CRPS* chronic regional pain syndrome

Repeated measures analysis will be used for the following:
Continuous variables measured at 3 months and 12 months include EQ-5D-5L (UI and VAS scores), pain on NRS (0–10) and radiographic measures (dorsal angulation, radial tilt, ulnar variance and articular step). These measurements will be analysed using analysis of variance (ANOVA) with repeated measuresCategorical variables measured at 3 months and 12 months include patient-reported treatment success (Likert) and patient-reported bother with appearance (Likert). See Additional file 1 for question format. These variables will be analysed by contingency table to compare the frequency of treatment success categories between the two randomised groups. Results will be displayed as odds ratio with 95% CIs (see Table 4 for example)

The observational group will be used to investigate potential selection bias. Baseline characteristics will be compared between the observational group and the randomised group (see Table 10 for example).

**Table 10 Tab10:** baseline characteristics for the randomised and observational arms of trial

Baseline measure		Randomised arm (*n*=__)	Observational arm (*n*=__)
Age (years), mean (range)			
Gender n (%)	Female		
	Male		
Fracture type n (%)	23A		
	23C		
Radiographic features, mean (SD)	Dorsal angulation (degrees)		
	Radial tilt (degrees)		
	Ulnar variance (mms)		
	Articular step (mms)		
Co-morbidities, n (%)	Diabetes? (Y/N)		
	Smoker? (Y/N)		
	Glucocorticoid treatment? (Y/N)		
	Osteoporosis treatment? (Y/N)		

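### Articular step is compared across all participants, although extra-articular (23A) fractures have no step; the comparison should be confined to 23C fractures

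*SAP article*

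**What the plan says.** The Inclusion criteria section admits "23A (extra-articular distal radius fracture) or 23C (complete articular distal radius fracture"). Its displacement thresholds for angulation, shortening and articular step are alternatives, so a 23A fracture can qualify on angulation or shortening alone.

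Articular step is one of four radiographic measures listed under Outcome variables. Under Study hypotheses, surgery is expected to bring all four closer to normal in patients aged 60 and older with displaced fractures, whatever the fracture type. Under Secondary analysis, repeated-measures ANOVA is assigned to "pain on NRS (0–10) and radiographic measures (dorsal angulation, radial tilt, ulnar variance and articular step"), among others. The same section adds: "Continuous outcomes will be reported by mean values as well as the MDs and 95% CIs". The Articular step row appears in Tables 4-7 and 11-13 under a single n per arm, as a mean (SD) with a mean difference.

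Fracture type is recorded at baseline. It appears in the baseline tables and in the imputation model for the primary outcome, but it plays no part in the analysis of step. It is not an allocation factor either: "Randomisation was stratified by site, and minimisation, adjusting for gender and age (60–74 years and > 74 years), was employed". In the observational study, treatment was chosen "according to patient and surgeon preference".

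**The concern.** An extra-articular fracture does not enter the joint, so it has no articular step for either treatment to reduce. Averaging step over 23A and 23C together mixes participants in whom the treatments can differ on this measure with participants in whom they cannot. A real benefit in 23C fractures would be reported as a smaller number, with less chance of reaching significance. A reader could then take a null row as evidence that surgery does not restore the joint surface better than casting, when part of the reason is the inclusion of fractures that do not involve that surface.

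The observational tables carry a second risk. Surgeons and patients may choose treatment partly on joint involvement. The 23C share could then differ between the treatment groups and produce a difference in mean step that is not a treatment effect, or hide one that is.

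**Working it through.** The plan gives no figure for articular step, so there is nothing of its own to reproduce. It does not state the 23C share or any step values either. Those below are assumptions.

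**Inputs**
- 164 randomised participants (Study population section), taken as 82 per arm with complete films.
- 23C share p: assumed 0.3, 0.5 or 0.7.
- Step in 23C: assumed mean 1.5 mm (SD 1.2) non-surgical and 0.8 mm (SD 1.0) surgical, a difference of 0.70 mm.
- Step in 23A: 0 mm, from the definition of extra-articular.

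**1. Dilution.** The mean in each arm is p × (mean in 23C) + (1 − p) × 0. The whole-group difference is therefore p × (difference in 23C):
- p = 0.3: 0.3 × 0.70 = 0.21 mm
- p = 0.5: 0.5 × 0.70 = 0.35 mm
- p = 0.7: 0.7 × 0.70 = 0.49 mm

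The proportion p holds whatever step values are assumed.

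**2. Power.** With zeros for 23A, the variance in an arm is p × SD² + p(1 − p) × mean². At p = 0.5:
- Non-surgical: 0.5 × 1.44 + 0.25 × 2.25 = 1.2825. Surgical: 0.5 × 1.00 + 0.25 × 0.64 = 0.66.
- All participants: SE = √((1.2825 + 0.66)/82) = 0.154; 0.35/0.154 = 2.27; power = Φ(2.27 − 1.96) ≈ 62%.
- 23C only, 41 per arm: SE = √((1.44 + 1.00)/41) = 0.244; 0.70/0.244 = 2.87; power = Φ(2.87 − 1.96) ≈ 82%.

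Simulation with gamma-distributed steps in 23C and a two-sample t test agrees with this:

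| 23C share | Difference, all | Power, all | Power, 23C only |
|---|---|---|---|
| 30% | 0.21 mm | 38% | 60% |
| 50% | 0.35 mm | 63% | 81% |
| 70% | 0.49 mm | 83% | 91% |

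With a smaller assumed effect (1.5 v 1.0 mm, SD 1.0 in both arms) the direction is the same: at a 50% share, 39% for all participants against 62% in 23C only.

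**3. Fracture mix in the randomised comparison.** The 23C share differs between arms by chance, with SD √(2p(1 − p)/82) = 0.072, 0.078 and 0.072 for the three shares. The whole-group variance in step 2 already contains this. Simulated with no treatment effect, the all-participant t test rejected in 5.0%, 4.7% and 4.9% of trials.

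**4. Fracture mix in the observational comparison.** Suppose 23C makes up 60% of the surgical group and 40% of the non-surgical group.
- No effect, mean step 1.25 mm in 23C under both treatments: (0.6 − 0.4) × 1.25 = 0.25 mm, a spurious difference against surgery.
- A true benefit of 0.5 mm in 23C (1.0 v 1.5 mm): 0.6 × 1.0 − 0.4 × 1.5 = 0, so the benefit disappears.

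**5. The plan's fallback.** Under Analysis principles, continuous data are shown by mean and mean difference "if normally distributed, otherwise by median and interquartile range". That does not help here. Where more than half of a group has a 23A fracture recorded as 0, its median step is 0 whatever happens in 23C.

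**The case against.** The strongest reply is that the all-participant mean is a legitimate estimand. The hypothesis covers all eligible patients, a step of 0 mm in an extra-articular fracture is a true value, and the population average is what an intention-to-treat summary gives. That stands in so far as the planned result would not be false. It would answer a less useful question with less power.

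It is also fair that little turns on this row. The plan sets importance thresholds for PRWE, DASH, EQ-UI, EQ-VAS and pain but none for step, and the sample size rests on PRWE alone. The power figures rest on assumed values, full follow-up and a t test, whereas the plan assigns step to repeated-measures ANOVA. Only the dilution identity is free of the assumed step values, and it still needs 23A to be recorded as 0.

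Two stronger readings are tempting and are not supported. A reader might infer from the absence of fracture type among the allocation factors that the randomised step comparison is biased. It is not: imbalance there is chance, it is already in the standard error, and the error rate is nominal. A reader might also infer that the 19 sites will code 23A differently, some as 0 and some as blank, leaving the row uninterpretable. Nothing in the article says so. It describes entry into one central database and an x-ray audit, and field coding is ordinarily left to data-collection documents that are not shown.

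**Conclusion.** The point holds as a minor one. The stated analysis of articular step covers all participants, although 23A fractures have no step by the plan's own definition. With 23A at 0, the reported difference is the 23C share times the effect in 23C, that is, 30% to 70% of it over the assumed range of shares. The loss of power is illustrative: roughly 63% against 81% at a 50% share, under the assumed step values, 82 per arm and a t test.

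In the randomised group the cost is dilution and extra variance, not bias. Confounding by fracture mix arises only in the observational tables, and only if the 23A/23C mix differs between treatments there, which the article does not report. One of four radiographic measures is affected. The PRWE primary analysis and the sample size are not.

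**What to change.** Before treatment allocation is unmasked, add a sentence to the repeated-measures paragraph of Secondary analysis stating that articular step is analysed in participants with a 23C fracture at baseline. In the Articular step rows of Tables 4-7 and 11-13, give a separate n per arm and footnote that 23A is not applicable. Keep dorsal angulation, radial tilt and ulnar variance in all participants.

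The cost is one sentence, a table footnote and a smaller n for that row; the participants left out carry no information on step. Fracture type is already collected and precedes treatment, so the restriction keeps the randomised comparison intact. In the observational tables it removes the confounding by 23A/23C mix, though not other differences between patients who chose each treatment.
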